### AML-Specific Dose Modifications for Drug-Related Hematologic Toxicities

If a subject with AML experiences hematologic toxicity during the study, the dose of ABBV-467 should be modified as indicated in [Table 4](#).

**Table 4. AML-Specific ABBV-467 Dose Modifications for Drug-Related Hematologic Toxicities**

| Treatment Cycle            | Efficacy Assessments | Hematology Results                                                                                                  | Action                             | Modifications                                                                                                                                      |
|----------------------------|----------------------|---------------------------------------------------------------------------------------------------------------------|------------------------------------|----------------------------------------------------------------------------------------------------------------------------------------------------|
| After Cycle 1 a | CRi
MLFS          | Incomplete count recovery                                                                                           | Delay upcoming cycle               | ABBV-467 should be interrupted to allow for ANC recovery from Day 29 until $ANC \geq 500/\mu L$ or up to 14 days (by Day 42), whichever is earlier |
| After Cycle 2              | CRi
MLFS          | New Grade 4 neutropenia lasting for more than 1 week (unless due to the underlying disease)                         | Delay upcoming cycle               | ABBV-467 dosing should be interrupted once cycle is completed until ANC is $\geq 500/\mu L$ (unless medically necessary to interrupt within cycle) |
| After Cycle 3              | CR
CRi
MLFS    | Subjects requiring interruption or delay of study drug administration for cytopenias (neutropenia/thrombocytopenia) | Reduce per-cycle ABBV-467 duration | ABBV-467 should be administered Days 1, 8, and 15 (but not Day 22) of each subsequent 28-day cycle                                                 |

AML = acute myeloid leukemia; ANC = absolute neutrophil count; CR = complete remission; CRi = complete remission with incomplete blood count recovery; MLFS = morphologic leukemia-free state; PLT = platelet

- a. Resistant disease or partial remission: there is no delay of next cycle. Once these subjects achieve CRi/MLFS, follow steps above in the sequence listed. CRi ( $ANC < 1,000/\mu L$  or  $PLT < 100,000/\mu L$ ); MLFS ( $ANC < 1,000/\mu L$  &  $PLT < 100,000/\mu L$ ).

## Tumor Lysis Syndrome

Subjects with MM with high tumor burden (e.g., high bone marrow plasma cell infiltration, plasma cell leukemia, or bulky plasmacytomas), rapidly increasing M-protein or light chains or high proliferative activity, plasmablastic morphology, or compromised renal function ( $CrCl < 50$  mL/minute) may be at higher risk of developing TLS. There is a potential risk for TLS in subjects with AML, especially in those with elevated leukocyte count, circulating blasts, elevated pretreatment lactate dehydrogenase levels, renal dysfunction, and dehydration. To mitigate the risk for TLS all subjects enrolled into the study will need TLS prophylaxis and monitoring. For subjects at higher risk for TLS, additional mitigation measures with more intensive laboratory monitoring and intervention should be implemented. Prophylactic reductions of potassium, inorganic phosphorus or uric acid above normal range are recommended prior to beginning study treatment and to be continued based on the ongoing risk of TLS. Please reference [Appendix F](#) for additional information on the evidence of TLS and [Appendix G](#) for initial management of electrolyte abnormalities and prevention of TLS.

During dose escalation, each subject should be hospitalized the night prior to C1D1 for hydration, treatment with uric acid-reducing agents, and monitoring. Tumor lysis syndrome laboratories will be obtained at 3 different time points: immediately prior to the first dose, 6 to 8 hours after the first dose, and approximately 24 hours after the first dose (on C1D2).

The subject may be discharged once the laboratory results on C1D2 are reviewed (approximately 24 hours after first dose) and confirm the absence of TLS. If discharged since first dose, subjects will be re-hospitalized the night prior to C1D8 for hydration, treatment with uric acid-reducing agents, and monitoring.

Tumor lysis syndrome prophylaxis and management for the second dose of ABBV-467 will be managed in the same manner as the first dose described above. Subjects who experience clinical or laboratory TLS, or other significant toxicity following the first or second dose of ABBV-467 should discuss the safety monitoring plan for subsequent doses of ABBV-467 with the AbbVie TA MD.

The Sponsor will review the totality of clinical and laboratory data on an ongoing basis and may provide additional recommendations regarding the need for subject monitoring, including either removing the need for, or extending required duration of, any hospitalization.

**Below are the minimum requirements for TLS prophylaxis and management for all subjects enrolled into the study.** All other prophylaxis and monitoring procedures for TLS will be implemented as per regional guidelines/institutional standards:

- All subjects must receive uric acid reducing agent, adequate oral and IV hydration as tolerated while monitoring the fluid status of the subject prior to and during the first cycle of treatment. The uric acid reducing agent, type of fluids and the rate of infusion will be determined by the investigator based on regional standards or institutional guidelines.
- TLS chemistry tests to be drawn (calcium, inorganic phosphorus, potassium, uric acid, and creatinine) on the first day of dosing and each day of a new dose at 0 (within 4 hours prior to dosing) and 6 – 8 hours post dose.
- Additional laboratory assessments may be performed, per investigator discretion, post-dose and up to 48 hours, if clinically indicated.

Abnormal chemistry tests should be corrected promptly. If a subject meets criteria for clinically significant laboratory or clinical TLS ([Appendix F](#)), institutional guidelines or recommendations in [Appendix G](#) should be followed, no additional doses should be administered until resolution. For continued dosing, monitor for evidence of TLS during study treatment, and manage abnormalities of serum creatinine, and electrolytes promptly.

### Hepatic Laboratory Abnormalities

Subjects should be monitored closely for hepatic-related laboratory abnormalities and AEs. In instances of new observations of hepatic laboratory abnormalities (i.e., ALT and/or AST  $> 1- < 3 \times \text{ULN}$  and/or total bilirubin  $< 2 \times \text{ULN}$ ), clinical chemistries should be re-tested within 48 to 72 hours.

An algorithm for monitoring and management of drug-induced liver injury in subjects with normal or elevated baseline ALT and/or AST (defined as the average of 2 screening measurements) is available in [Appendix H](#) and should be used for study drug-related toxicity management. Guidelines should be followed for all subjects regardless of baseline liver function laboratory values. Hy's law is defined as ALT/AST and bilirubin in the normal reference range prior to study drug dosing, with subsequent development of ALT or AST  $\geq 3 \times \text{ULN}$  along with total bilirubin  $> 2 \times \text{ULN}$ , without findings of cholestasis

(elevated serum ALP) and with no alternative explanation. Any suspected cases of Hy's Law will require clinical review and confirmation.

Any increase in ALT and/or AST that is  $\geq 3 \times \text{ULN}$  but  $< 5 \times \text{ULN}$ , the dose will be held until the toxicity resolves to Grade 1 or lower, or to baseline if the toxicity was  $> \text{Grade 1}$  at the time of study entry. Upon toxicity resolution, the subject may restart study drug at a dose that is at least 33% lower than the previous dose. For ALT and/or AST increase  $\geq 5 \times \text{ULN}$  study drug may be restarted only if another etiology is identified and liver enzymes return to baseline.

In the event of hepatic abnormalities, documentation which captures relevant clinical signs and symptoms should be completed by the site in the source records and corresponding eCRF(s). In addition, for hepatic abnormalities, this should include imaging as clinically indicated (e.g., abdominal ultrasound, endoscopic retrograde cholangiopancreatography) to exclude alternative etiologies of liver injury (with full reports made available).

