#### Demographic and Laboratory Assessments

- ✓ 2. At least 18 years old.
- ✓ 3. Eastern Cooperative Oncology Group (ECOG) performance status 0, 1, or 2.
- ✓ 4. **Laboratory values** meeting the following criteria during the screening period prior to first dose of study drug:
  - For subjects with AML, the following hematologic parameter requirements are not applicable. For subjects with MM, subjects must have adequate hematologic function, defined as follows:
    - Absolute neutrophil count  $\geq 1000/\text{mm}^3$ ;
    - Platelet count  $\geq 75,000/\text{mm}^3$ ;
    - Hemoglobin  $\geq 8 \text{ g/dL}$ ;
  - Serum alanine aminotransferase (ALT)  $\leq 2.5 \times$  upper limit of normal (ULN);
  - Serum aspartate aminotransferase (AST)  $\leq 2.5 \times$  ULN;
  - Total bilirubin  $\leq 1.5 \times$  ULN (subject with documented Gilbert's syndrome may have a total bilirubin  $>1.5 \times$  ULN);
  - Amylase  $\leq 2 \times$  ULN;
  - Lipase  $\leq 2 \times$  ULN;
  - Creatinine clearance (CrCl)  $\geq 60 \text{ mL/min}$ , measured by 24-hour urine collection or calculated using the Cockcroft-Gault formula.
- ✓ 5. Echocardiogram with ejection fraction  $\geq 50\%$  and no other clinically significant finding that would increase the subject's susceptibility to cardiac toxicity.
- ✓ 6. No clinically relevant or significant ECG abnormalities, including ECG with QT interval corrected for heart rate (QTc) using Fridericia's formula (QTcF)  $> 450 \text{ msec}$  (males) or  $> 470 \text{ msec}$  (females).
- ✓ 7. Willingness and ability to comply with procedures required in this protocol.

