## 6.3 Dose-Limiting Toxicity

---

Dose-limiting toxicity for dose escalation purposes will be determined on events that occur during the first 28-day cycle.

Any AE of Grade 3 or higher will be considered a DLT, unless toxicity can solely be attributed to the underlying disease, with the following clarifications. Adverse events of any grade resulting in discontinuation of study drug will be considered a DLT. Missing any dose as a result of toxicity unexplained by the underlying disease will also be considered a DLT.

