## APPENDIX H. MONITORING AND MANAGEMENT OF DRUG-INDUCED LIVER INJURY

Hepatic abnormalities will be graded based on the criteria in the table below, adapted from CTCAE v5.0.

| MedDRA SOC     | CTCAE Term    | Grade 1                                                                                               | Grade 2                                                                                              | Grade 3                                                                                            | Grade 4                                                                                    | Grade 5 |
|----------------|---------------|-------------------------------------------------------------------------------------------------------|------------------------------------------------------------------------------------------------------|----------------------------------------------------------------------------------------------------|--------------------------------------------------------------------------------------------|---------|
| Investigations | ALT increased | > ULN –
3 × ULN if
baseline was
normal; 1.5 -
3 × baseline if
baseline was
abnormal | > 3 - 5 × ULN if
baseline was
normal; > 3.0 -
5.0 × baseline if
baseline was
abnormal | > 5 - 20 × ULN if
baseline was
normal; > 5 -
20 × baseline if
baseline was
abnormal | > 20 × ULN if
baseline was
normal;
> 20 × baseline
if baseline was
abnormal | -       |
| Investigations | AST increased | > ULN -
3 × ULN if
baseline was
normal; 1.5 -
3 × baseline if
baseline was
abnormal | > 3 - 5 × ULN if
baseline was
normal; > 3 -
5 × baseline if
baseline was
abnormal     | > 5 - 20 × ULN if
baseline was
normal; > 5 -
20 × baseline if
baseline was
abnormal | > 20 × ULN if
baseline was
normal;
> 20 × baseline
if baseline was
abnormal | -       |

ALT = alanine aminotransferase; AST = aspartate aminotransferase; CTCAE = Common Terminology Criteria for Adverse Events; MedDRA = Medical Dictionary for Regulatory Activities; SOC = system organ class; ULN = upper limit of normal

An algorithm for monitoring and management of drug-induced liver injury in subjects with normal or elevated baseline ALT (defined as the average of 2 screening measurements) is presented in the table below.

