| ≥ 3 -
< 5 × ULN                | Normal
(TBL
< 2 × baseline in
subjects with
Gilbert
syndrome) | Absent                | 
 
Hold treatment
 
Monitor LFTs every 3 - 5 days
 
Restart study drug at ≥ 33% dose reduction if LFTs return to baseline or < 3 × ULN (permanently discontinue treatment if LFTs become abnormal with treatment at reduced dose)
 
 |                                                                                                                                                                                                                                                                                                                                                                                    |
| ≥ 3 -
< 5 × ULN                | > 2 × ULN and/or
INR > 2.0                                                | Absent or
present  | 
 
Permanently discontinue treatment
 
                                                                                                                                                                                                               | 
 
Consider inpatient evaluation
 
                                                                                                                                                                                                                                                                                                    |
| ≥ 5 × ULN                         | Any                                                                          | Absent or
present  | 
 
Permanently discontinue treatment unless another etiology is identified and liver enzymes return to baseline
 
                                                                                                                                    | 
 
Monitor LFTs every 1 - 2 days
 
Consider hepatology consultation
 
                                                                                                                                                                                                                                                          |

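### For subjects who enter with ALT/AST above ULN, Section 6.2 and Appendix H give opposite restart decisions on the same value, and the outcome can feed the Cycle 1 DLT count

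*Protocol*

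**What the plan says.** - **Entry.** Criterion 4 in Section 5.1 allows ALT and AST up to and including 2.5 x ULN, so some subjects may start above ULN.
- **Trigger.** Section 6.2 (Hepatic Laboratory Abnormalities) holds at 3 to <5 x ULN. At 5 x ULN or more it allows restart only if another cause is found and enzymes are back at baseline. It adds: "Guidelines should be followed for all subjects regardless of baseline liver function laboratory values".
- **Release, Section 6.2.** "the dose will be held until the toxicity resolves to Grade 1 or lower", or to baseline for a toxicity that was above Grade 1 at entry. Restart is at a reduced dose.
- **Grading, Appendix H.** "Hepatic abnormalities will be graded based on the criteria in the table below, adapted from CTCAE v5.0". For an abnormal baseline, Grade 1 is 1.5 to 3 x baseline, Grade 2 is above 3 to 5 x baseline, and Grade 3 is above 5 to 20 x baseline.
- **Release, Appendix H.** In the 3 to <5 x ULN row (bilirubin normal, no symptoms), restart at a reduced dose needs enzymes at baseline or below 3 x ULN. Section 6.2 itself sends sites to this algorithm.
- **Stop, Appendix H.** At 5 x ULN or more: "Permanently discontinue treatment unless another etiology is identified and liver enzymes return to baseline".
- **DLT, Section 6.3.** "Adverse events of any grade resulting in discontinuation of study drug will be considered a DLT". A dose missed for toxicity that the disease does not explain also counts. Section 6.1 makes a laboratory change an AE when it meets the Section 6.2 criteria.
- **Baseline.** Section 6.2 and Appendix H use the mean of two screening values. Operations Manual Section 3.15 uses the most recent value before the first dose.

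**The concern.** The hold starts on one scale (multiples of ULN) and, in Section 6.2, ends on another (grade, which for these subjects means multiples of baseline). A rule built that way can be satisfied at the moment it is invoked. Appendix H, which governs the same event, ends the hold on the ULN scale. A site following Section 6.2 and a site following Appendix H can then treat the same subject and value differently, one restarting and the other holding.

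This concerns subject safety first. It also concerns the primary objective, because in Cycle 1 the choice decides whether a weekly dose is missed. A missed dose is either a DLT (numerator of Table 1) or, if not scored as one, makes the subject non-evaluable under Section 4.1, which requires all planned Cycle 1 doses (denominator).

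**Working it through.** **The plan's own figure first.** With target 0.25 and alternatives 0.6 x 0.25 = 0.15 and 1.4 x 0.25 = 0.35, the BOIN boundaries are:

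- escalate: ln(0.85/0.75) / ln[(0.25 x 0.85)/(0.15 x 0.75)] = 0.1968
- de-escalate: ln(0.75/0.65) / ln[(0.35 x 0.75)/(0.25 x 0.65)] = 0.2984

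Section 4.1 states 0.197 and 0.298, and the Table 1 escalation and de-escalation counts follow. The design arithmetic is sound.

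**Crosswalk between the two scales.** For a baseline of B x ULN with B above 1, the hold threshold is 3/B x baseline and the stop threshold is 5/B x baseline. Grade 2 begins above 3B x ULN and Grade 3 above 5B x ULN.

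| Baseline (x ULN) | 3 x ULN: multiple of baseline, grade | 5 x ULN: multiple of baseline, grade | Grade 2 above (x ULN) | Grade 3 above (x ULN) |
|---|---|---|---|---|
| 1.20 | 2.50, Grade 1 | 4.17, Grade 2 | 3.60 | 6.00 |
| 1.50 | 2.00, Grade 1 | 3.33, Grade 2 | 4.50 | 7.50 |
| 1.67 (= 5/3) | 1.80, Grade 1 | 3.00, Grade 1 | 5.00 | 8.33 |
| 2.00 | 1.50, Grade 1 | 2.50, Grade 1 | 6.00 | 10.00 |
| 2.50 | 1.20, below Grade 1 | 2.00, Grade 1 | 7.50 | 12.50 |

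Four results follow.

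1. For any B above 1, 3/B is below 3, so a value of 3 x ULN is Grade 1 or lower and the Section 6.2 release is already met. The return-to-baseline limb does not help: an entry value of at most 2.5 x ULN is not above Grade 1 on either scale.
2. The whole hold band is Grade 1 or lower when 5/B is at most 3, that is, B of at least 5/3 = 1.67. For B between 1 and 1.67 the upper part of the band is Grade 2.
3. The stop at 5 x ULN falls at Grade 1 for B from about 1.67 to 2.5 and at Grade 2 for lower abnormal baselines.
4. For a normal baseline the scales agree except at exactly 3.0 and 5.0 x ULN, so the problem is confined to raised baselines.

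**The two releases on one value.** Baseline 1.5 x ULN, current value 4 x ULN: 4/1.5 = 2.67 x baseline, Grade 1. Section 6.2: release condition met. Appendix H: 4 is neither baseline nor below 3 x ULN, so the hold continues.

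**Effect of the baseline definition.** Suppose the screening mean is 1.2 and the last pre-dose value is 1.5 x ULN (illustration). The same 4 x ULN is 4/1.2 = 3.33 x baseline (Grade 2) or 2.67 x baseline (Grade 1). The Section 6.2 release then depends on which definition is used.

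**Route into Table 1.** One DLT in 2 or 3 evaluable subjects is 0.50 or 0.33, above 0.298, and Table 1 reads de-escalate. The frequency of such events is not given. As an assumption only: if they added an independent 5%, 10% or 20% per subject to a true DLT rate of 0.15, the chance of at least one DLT in 3, which is 1 - [0.85 x (1 - q)]^3, would go from 0.386 (q = 0) to 0.473, 0.552 or 0.686.

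**The case against.** The best defence is that ULN limits for all subjects are chosen openly. The dog study in Supplementary Table S7 reports marked transaminase rises and hepatocyte necrosis, so absolute limits are plausible caution in a first-in-human trial. Grades describe severity and limits trigger action, and using both is not in itself a contradiction. That stands: the triggers are not an error. It does not explain why one release uses grade and the other uses ULN.

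A reader might go further in four ways that the documents do not support.

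- *That the release is simply already met when the hold starts.* This is true of Section 6.2 alone. The Appendix H condition is never met at the start of a hold at 3 x ULN or above, unless the value is back at a baseline that entry caps at 2.5.
- *That subjects are stopped for a Grade 0 change.* The stop is never below Grade 1, is Grade 1 only from about 1.67 x ULN upward, and carries the exception for another cause with return to baseline.
- *That a hold is a DLT.* It becomes one only through a missed Cycle 1 dose not explained by the disease. Dosing is weekly, enzymes are rechecked every 3 to 5 days during a hold, and Days 8, 15 and 22 have a one-day window, so some holds would cost no dose.
- *That the RP2D is pushed down.* No prevalence of raised baselines is given, Section 4.1 lets escalation decisions take in all available information and intermediate doses, and the RP2D rests on safety, efficacy, PK and PD together.

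**Conclusion.** The point holds in a limited form. For subjects entering with ALT/AST above 1 and up to 2.5 x ULN, two stated rules for the same event disagree on when dosing may resume: at the bottom of the hold band for every such baseline, and throughout the band from about 1.67 x ULN. At the entry limit the hold begins at 1.2 x baseline, below Grade 1, and the stop at 2.0 x baseline, Grade 1.

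Read literally, Section 6.3 lets such low-grade events count as DLTs in Cycle 1, by a stop at any grade or by a missed dose. Their number cannot be estimated from the documents, so no bias in dose selection is shown. No sample size or BOIN figure is affected. The conclusion rests on reading grade as Appendix H defines it and on taking baseline above ULN as abnormal. The inconsistency should be corrected, because it concerns restart of treatment after a liver signal.

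**What to change.** The sponsor's safety team should:

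- reconcile the release conditions in Section 6.2 and Appendix H for subjects with raised baseline ALT/AST, so that one value gives one decision;
- reconcile the baseline definition between Section 6.2 and Appendix H on one side and Operations Manual Section 3.15 on the other;
- state in Section 6.3 how a hold or stop triggered at baseline-adjusted Grade 1 or lower is scored for DLT, and whether a subject who misses a dose for that reason remains DLT-evaluable.

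Which release rule applies, and whether limits and grades share a scale, is the safety team's clinical decision. No threshold is suggested here. The cost is wording in Sections 6.2 and 6.3, Appendix H and the Operations Manual. It needs no extra visits, samples or subjects.

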|------------------------------------------------------------------------------------------------------------------------------------------------------------------------------------------------------------------------|--------------------------------|
| All AEs that meet DLT criteria, per protocol Section 6.3, Dose-Limiting Toxicity                                                                                                                                       | Dose-Limiting Toxicity eCRF    |
| Discontinuation or interruption of study drug due to a hepatic-related AE
A hepatic-related SAE
Clinically significant hepatic AEs
ALT or AST $\geq 3 \times$ ULN along with total bilirubin $> 2 \times$ ULN | Hepatic AE eCRF                |
| All AEs of infusion related reaction regardless of causality                                                                                                                                                           | Infusion Related Reaction eCRF |
| AEs of overdose, abuse, off-label use, misuse, medication error, occupational exposure                                                                                                                                 | Special Safety Situations eCRF |
| Per protocol Section 6.2, Toxicity Management                                                                                                                                                                          | Tumor Lysis Syndrome eCRF      |

AE = adverse event; eCRF = electronic case report form; SAE = serious adverse event; ULN = upper limit of normal

If an AE, whether associated with study drug or not, meets any of the following criteria, it is to be reported to AbbVie clinical pharmacovigilance as a SAE within 24 hours of the site being made aware of the SAE (refer to Section 4.3 of the Operations Manual for reporting details and contact information):

|                                                           |                                                                                                                                                                                                                                                                                                                              |

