### Non-hematologic DLTs (regardless of attribution)

- Grade 3 mucositis, nausea, vomiting, or diarrhea will only be considered a DLT if they require total parenteral nutrition, tube feeding, or prolonged hospitalization (> 72 hours).
- Any Grade 4 non-hematologic laboratory abnormality.
- Any instance of an AE that meets the definition of Hy's Law.

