| Treatment-Emergent ALT and/or AST | Treatment-Emergent TBL and/or INR                                            | Symptoms a | Action                                                                                                                                                                                                                                                                                            | Assessment/Management                                                                                                                                                                                                                                                                                                                                                              |
|-----------------------------------|------------------------------------------------------------------------------|-----------------------|---------------------------------------------------------------------------------------------------------------------------------------------------------------------------------------------------------------------------------------------------------------------------------------------------|------------------------------------------------------------------------------------------------------------------------------------------------------------------------------------------------------------------------------------------------------------------------------------------------------------------------------------------------------------------------------------|
| > 1 -
< 3 × ULN                | Normal
(TBL
< 2 × baseline in
subjects with
Gilbert
syndrome) | Absent                | 
 
Continue treatment; or consider holding treatment for concerning lab value trend
 
Monitor LFTs every 3 - 5 days
 
Follow-up for symptoms
 
                                                                                         | 
 
Rule out viral etiology, hepatic dysfunction related to underlying malignancy, and/or other drug-induced transaminase elevations
 
Consider ultrasound
 
Consider MRCP if ultrasound non-diagnostic
 
Limit/discontinue hepatotoxic medications (assess acetaminophen, dietary supplement, and alcohol use)
 
 |

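### Section 6.2 lets any ALT/AST rise of 3 to below 5 × ULN restart at a reduced dose, while Appendix H stops part of that band permanently, and no text says which prevails

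*Protocol*

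**What the plan says.** The Hepatic Laboratory Abnormalities text in Section 6.2 first points to the Appendix H algorithm, which "should be used for study drug-related toxicity management", and says the guidelines apply to all subjects whatever their baseline liver values. It then gives its own rule. "Any increase in ALT and/or AST that is" at least 3 but below 5 × ULN leads to a dose hold until Grade 1 or baseline, after which: "Upon toxicity resolution, the subject may restart study drug at a dose that is at least 33% lower than the previous dose". For rises of 5 × ULN or more it is stricter: restart only if another cause is found and enzymes return to baseline.

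Appendix H splits the 3 to below 5 × ULN band by a column headed "Treatment-Emergent TBL and/or INR" and by symptoms.

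- Restart row: TBL normal (or below 2 × baseline in Gilbert syndrome) and symptoms absent. Hold, then "Restart study drug at ≥ 33% dose reduction if LFTs return to baseline or" below 3 × ULN. If liver tests become abnormal again at the reduced dose, treatment ends.
- Stop row: TBL above 2 × ULN and/or INR above 2.0, symptoms absent or present. The action is to "permanently discontinue treatment", with no exception.

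**The concern.** The same subject can receive two opposite instructions. Take ALT at 4 × ULN with TBL above 2 × ULN. Section 6.2 allows a restart after resolution; Appendix H ends treatment. A site working from the body text could re-expose someone the appendix withdraws.

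This is a first-in-human study, and Supplementary Table S7 lists the liver among the target organs in the dog study, with marked transaminase rises and hepatocyte necrosis. Combined enzyme and bilirubin or INR changes are therefore what the liver rules most need to state without ambiguity.

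**Working it through.** No sample-size, power or error-rate figure is involved, so the check sets the two texts side by side over the same enzyme range.

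| ALT/AST | TBL, INR, symptoms | Section 6.2 | Appendix H | Result |
|---|---|---|---|---|
| 3 to < 5 × ULN | TBL normal (or < 2 × baseline in Gilbert syndrome), INR not > 2.0, no symptoms | Hold, may restart at ≥ 33% lower dose | Hold, restart at ≥ 33% lower dose | Agree |
| 3 to < 5 × ULN | TBL > 2 × ULN and/or INR > 2.0, with or without symptoms | Hold, may restart | Permanent stop | Contradict |
| 3 to < 5 × ULN | TBL normal, INR not > 2.0, symptoms present | Hold, may restart | Does not fit the restart row | Section 6.2 looser |
| 3 to < 5 × ULN | TBL above normal but not > 2 × ULN, no Gilbert syndrome, INR not > 2.0 | Hold, may restart | Does not fit the restart row | Section 6.2 looser |
| ≥ 5 × ULN | Any | Restart only with another cause and return to baseline | Stop unless another cause and return to baseline | Agree |

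The direct contradiction is confined to the second line. The third and fourth lines show that Section 6.2 is also broader than the restart row without meeting the stop row. The last line shows that Section 6.2 carries an Appendix H restriction into the body for the upper band. For the lower band it carries over the restart and leaves out the stop.

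**Do other provisions stop the subject anyway?**

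- Section 6.1 sends ALT or AST of at least 3 × ULN with TBL above 2 × ULN to the "Hepatic AE eCRF". That records the case.
- Section 6.2 asks for clinical review and confirmation of suspected Hy's Law cases.
- Section 6.3 makes "Any instance of an AE that meets the definition of Hy's Law" a DLT.

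None of these by itself tells the site to end that subject's dosing. The protocol's Hy's Law definition also requires normal ALT/AST and bilirubin before dosing, whereas eligibility admits ALT/AST up to 2.5 × ULN and bilirubin up to 1.5 × ULN. Subjects who enter with abnormal values therefore fall outside the Hy's Law provisions, and so does an isolated INR above 2.0.

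**Would the markers be available?** TBL is on the routine central chemistry panel (Operations Manual Table 6), drawn at every dosing visit. PT/INR is a local test (Table 7) fixed at Screening and Final Visit in Appendix D. In between, Operations Manual 3.15 repeats it on Day 1 of each cycle for vitamin K antagonist users, or on clinical indication. No text ties an INR draw to an enzyme threshold.

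**The case against.** The strongest reply is that Section 6.2 already makes Appendix H the working algorithm, for all subjects, just before its own rule. The restart is also a permission that depends on resolution, so a site that follows the stop row breaks nothing in Section 6.2. That much stands, and a reader who inferred that the protocol offers no route to the stop would be wrong. It does not remove the contradiction. The restart sentence comes after the pointer, covers any increase in the band and makes no exception, and no clause says which text governs.

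Second, general safeguards exist. Section 5.5 allows withdrawal for clinically significant laboratory results, as judged by the investigator or the sponsor's medical director. Operations Manual 3.15 lists repeat testing, follow-up, discontinuation and sponsor contact for significant out-of-range values. These apply to bilirubin and INR alike, but they are discretionary, whereas the stop row is not.

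Third, a reader might infer that the INR arm of the stop row cannot work because coagulation is not scheduled on treatment. The documents do not support that. A panel may be drawn on clinical indication, and an enzyme rise under an algorithm with an INR criterion is a natural indication. The lack of an explicit order contradicts nothing; adding one is a refinement.

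**Conclusion.** The inconsistency holds and should be corrected. It is a direct contradiction in one cell (ALT/AST 3 to below 5 × ULN with treatment-emergent TBL above 2 × ULN and/or INR above 2.0). It is a looser rule in two neighbouring cells: symptomatic subjects, and subjects without Gilbert syndrome whose TBL is raised but not above 2 × ULN.

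The size is minor. Dosing is held first, enzymes must resolve, the dose falls by at least 33%, and Appendix H ends treatment if liver tests become abnormal again at the reduced dose. The documents give no frequency for these events, so no rate of wrongly restarted subjects can be stated.

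A reader might also infer that escalation decisions are affected. The documents do not establish that. Section 6.3 already counts as a DLT any Cycle 1 dose missed through toxicity not explained by the disease, and any Hy's Law case, so in those cases the count does not depend on which liver text was followed. No effect on DLT counts, planned analyses or sample size is claimed.

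The conclusion assumes that sites act on the body text as written and that the sponsor intends the Appendix H stop to be binding.

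**What to change.** In Section 6.2, keep the restart sentence for the 3 to below 5 × ULN band and add to it: *only where the Appendix H restart row applies; if treatment-emergent TBL > 2 × ULN and/or INR > 2.0, treatment is stopped permanently per Appendix H.* Referring to the restart row, and not only excluding the stop-row values, also closes the two neighbouring cells. The Appendix H thresholds stay as they are. The cost is one clause in an amendment.

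One drafting detail needs the medical lead. Eligibility admits documented Gilbert syndrome with bilirubin above 1.5 × ULN. At a baseline of 1.5 × ULN, twice baseline is 2 × 1.5 = 3 × ULN, so a value between 2 and 3 × ULN meets the Gilbert condition of the restart row and also exceeds the stop-row figure. The amendment should say which applies.

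Optional and secondary: state in Appendix H that a local PT/INR is drawn with the repeat liver tests whenever ALT/AST reaches 3 × ULN or more, with a line on how INR is read in vitamin K antagonist users. This costs one extra local blood tube per event, at laboratories already used for this test, and the fixed visits in Appendix D need not change.
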